## Abstract

**Background**: The gut microbiome is crucial in sustaining intestinal balance and general health. Following rectal cancer surgery, the creation of a diverting stoma to protect the anastomosis results in a defunctioned colon, leading to dysbiosis. The effect of probiotic intake on gut dysbiosis following ileostomy repair remains uncertain. Thus, this study aims to determine the changes in gut microbiota based on the intake of probiotics after diverting stoma repair. **Methods**: This single-center, parallel, prospective pilot study will include patients with primary rectal cancer planning to undergo a diverting stoma during rectal cancer surgery. The study will comprise 20 patients, with 10 patients receiving synbiotics after stoma repair and 10 patients not receiving probiotics. The primary endpoint is the change in the gut microbiota of the resting colon based on the intake of probiotics, assessed through fecal testing at the following time points: before bowel resection, immediately after diverting stoma repair, and 3 weeks after diverting stoma repair. Changes in gut microbiota will be evaluated using alpha- and beta-diversity analyses based on 16S rRNA sequencing of fecal samples. **Discussion**: This study is the first prospective cohort trial investigating changes in the gut microbiota of the resting colon based on oral probiotic administration in patients undergoing diverting stoma repair. This trial is anticipated to clarify the impact of probiotic intake in these patients. **Trial registration**: Clinical Research Information Service (CRIS) of the Republic of Korea, KCT0008392, Registered on 27 April 2023.

## 1. Background

Gut microbiota represents a diverse community of microorganisms residing in the gastrointestinal tract, including viruses, bacteria, fungi, archaea, and protozoa [1,2]. Gut microbiota is essential in human health, serving immunological, metabolic, and gut-protective functions and influencing not only the intestinal system but also the pancreas, liver, and brain [2,3]. Dysbiosis, defined as an alteration in the composition or function of the gut microbiota, is implicated in the progression of numerous diseases [1,4].

In patients undergoing rectal resection for rectal cancer, a diverting stoma is often performed to reduce the risk and severity of anastomotic leakage [5,6]. During the period of maintaining the diverting stoma, the defunctioned colon experiences a deficiency in short-chain fatty acids and butyrate derived from bacteria, changes in the colonic mucosa, and a lack of oxidative substrates [7,8,9]. These changes cause gut dysbiosis characterized by a reduced diversity of bacteria, an increase in pathogenic bacteria, and a decrease in beneficial bacteria [10]. Subsequently, dysbiosis, alongside functional and structural alterations in the colon, may contribute to Clostridium difficile infection or postoperative ileus after ileostomy reversal [11,12].

Probiotics are live microorganisms aimed at promoting gut health [13]. Recent studies in colorectal cancer patients have shown that probiotics colonize the colonic mucosa, influencing the local immune responses and gut microbiota [14,15]. Additionally, probiotics alleviate postoperative symptoms and induce modification in the microbiota and inflammatory markers following surgery [16,17,18]. A recent meta-analysis reported that perioperative probiotics in colorectal cancer significantly reduced postoperative infectious complications and shortened hospital stay [19]. Furthermore, regarding dysbiosis, probiotic supplementation has been increasingly recommended as a strategy for restoring microbial balance [20,21]. However, previous studies attempted to determine the effectiveness of probiotics following stoma repair, but no significant differences were found in patients’ subjective quality of life, as assessed by questionnaires [22,23].

We hypothesized that the intake of probiotics would mitigate dysbiosis by influencing the microbiota of the defunctioned colon. However, this effect was not identified using subjective questionnaires. Therefore, this study aims to evaluate whether probiotic intake could influence gut microbiota composition and diversity following diverting ileostomy reversal by analyzing changes in the microbiota through fecal testing.

## 2. Methods

### 2.1. Trial Design

This single-center, parallel, prospective cohort trial with a 1:1 allocation ratio will compare patients receiving and not receiving probiotics at the time of stoma repair. This study will be assessed using the SPIRIT (Standard Protocol Items: Recommendations for Interventional Trials) checklist [24]. Figure 1 presents the study flow, including the intervention and assessment.

### 2.2. Eligibility

Patients eligible for this clinical trial will be enrolled at the Chonnam National University Hwasun Hospital in the Republic of Korea. Eligible patients include individuals with primary rectal cancer without distant metastases, those aged > 20 years, and patients who sign a consent form agreeing to enroll in this study. Exclusion criteria comprise patients requiring emergency surgery due to intestinal obstruction or perforation, those who have already undergone ostomy surgery, patients taking antibiotics for a prolonged period, and pregnant women.

### 2.3. Participants

All patients with rectal cancer who visit our outpatient clinic will be closely monitored to ensure their eligibility. Once eligibility is confirmed, the surgeon responsible for each included patient will explain this study during their outpatient clinic visit and obtain informed consent.

Given the absence of previous studies examining changes in the gut microbiota of the resting colon following ileostomy reversal, a sample size calculation was not performed. Therefore, this study was designed as a pilot trial, and we anticipated that a sample of 20 patients would be sufficient to assess the changes in microbiota based on the intake of probiotics after ileostomy repair. According to the order of patient enrollment, the first 10 consecutive patients will be assigned to the probiotic group, while the next 10 patients will be assigned to the control group. The participants will be enrolled by the surgeon at each outpatient clinic, and probiotics will be provided by a designated researcher.

At the initial outpatient visit, an assessment will be conducted to confirm eligibility based on the inclusion criteria, followed by obtaining informed consent. All patients will undergo rectal resection with loop ileostomy as previously performed. The timing of ileostomy reversal will be determined based on the necessity of chemotherapy. The first fecal test will be performed before rectal resection, and the second fecal test will be performed during the first bowel movement after ileostomy repair. Patients in the experimental group will take probiotics for 3 weeks starting from the second fecal test, whereas patients in the control group will be observed for 3 weeks without taking probiotics. Afterward, the third fecal test will be performed at the next outpatient visit. Additionally, blood tests, including complete blood count (neutrophil, monocyte, lymphocyte, hemoglobin, and platelets), albumin, and C-reactive protein, will be performed to identify changes in inflammatory markers. Table 1 demonstrated the comprehensive schedule of assessments.

### 2.4. Interventions

The synbiotic powder contains eight probiotic strains: *Bacillus subtilis* IDCC 1101, *Lactobacillus sporogenes* IDCC 1201, *Clostridium butyricum* IDCC 1301, *Lactobacillus rhamnosus* IDCC 3201, *Lactobacillus plantarum* IDCC 3501, *Bifidobacterium breve* IDCC 4401, *Bifidobacterium animalis subspecies lactis* IDCC 4301, and *Lactobacillus johnsonii* IDCC 9203 (Ildong Bioscience Co. Ltd., Pyeongtaek, Republic of Korea). Additionally, it includes prebiotics (organic galactooligosaccharide and chicory dietary fiber), vitamins, zinc, calcium, and citric acid. This multi-strain probiotic powder will be administered once daily for 3 weeks. Each sachet contains 2 g of product, and participants will take one sachet once daily for 3 weeks. Participants can withdraw from the study at any time, for any reason, without facing any consequences. If a participant meets exclusion criteria that were previously unrecognized or develops a critical medical condition that renders them ineligible, the researcher may decide to discontinue their participation in the study. We will provide sufficient synbiotics in extra amounts and remind participants several times to ensure consistent daily intake. Because antibiotics can influence the gut microbiome, we will educate participants to limit their use and monitor it at each visit. Participants will be encouraged to maintain their usual dietary habits, although no strict dietary intervention will be applied. The control group will be managed according to existing treatment protocols. We will provide appropriate medical treatment for adverse events related to the research process and compensate it according to the regulations established by our institution.

### 2.5. Outcomes

The primary outcome is changes in the gut microbiota based on the intake of probiotics at the following time points: before bowel resection, immediately after diverting stoma repair, and 3 weeks after diverting stoma repair. Genomic DNA will be extracted from bacterial samples in patients’ feces using the QIAamp DNA Stool MiniKit (Qiagen^®^, Hilden, Germany). The library will be prepared according to the 16S Metagenomic Sequencing Library Preparation Illumina Protocol. Amplification of the V3–V4 region of 16S rRNA will be performed, followed by a polymerase chain reaction. After the quality assessment of the final library, the DNA quantity will be determined using the Qubit (Thermo Fisher Scientific Inc., Waltham, MA, USA) and Agilent Bioanalyzer 1000 (Agilent, Santa Clara, CA, USA). The methods for fecal microbiota analysis will follow a previously established procedure [25]. The EZBioCloud (ChunLab, Inc., Seoul, Republic of Korea) will be used to analyze the metagenome. To evaluate within-sample richness and evenness, the Shannon and Simpson indices will be applied, while dissimilarities between samples will be assessed using the Jensen–Shannon divergence and generalized UniFrac distance. We will analyze the pattern of changes to evaluate whether a 3-week course of probiotics alleviates dysbiosis, observed after ileostomy repair, and how it differs from the gut microbiota composition identified prior to the initial surgery. Alpha- and beta-diversity analyses will be conducted, along with an assessment of the proportions of beneficial and harmful bacteria [10].

The secondary outcomes include changes in inflammatory markers and differences in gut microbiota composition based on chemotherapy. Changes in inflammatory markers will be analyzed by comparing various ratios of neutrophils, lymphocytes, albumin, and C-reactive protein. The relationship between probiotic intake and inflammatory markers will be examined to explore the potential anti-inflammatory effects of probiotics following ileostomy repair. Additionally, gut microbiota composition will be compared between patients who underwent chemotherapy before stoma repair and those who did not.

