### 2.8. Statistical Methods

To compare categorical variables, the χ^2^ or Fisher’s exact test will be applied, while continuous variables will be examined by conducting Student’s *t*-test or the Mann–Whitney U-test. To evaluate statistical significance of alpha and beta diversities, the Kruskal–Wallis test and permutational multivariate analysis of variance (PERMANOVA) will be performed. A *p*-value of less than 0.05 will be considered statistically significant for all variables with. Statistical analyses will be conducted using SPSS version 27.0 (IBM Inc., Armonk, NY, USA).

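### PERMANOVA, the test named for beta diversity, shows only whether groups of samples differ, not whether patients moved toward or away from their own pre-resection composition

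*Protocol article*

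**What the plan says.** Section 2.5 (Outcomes) says the pattern of changes will be analysed to "evaluate whether a 3-week course of probiotics alleviates dysbiosis, observed after ileostomy repair", and to show "how it differs from the gut microbiota composition identified prior to the initial surgery". Three kinds of measure are planned:

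- within-sample diversity by the Shannon and Simpson indices;
- between-sample dissimilarity: "dissimilarities between samples will be assessed using the Jensen–Shannon divergence and generalized UniFrac distance";
- group-level taxa, "along with an assessment of the proportions of beneficial and harmful bacteria".

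Section 2.8 (Statistical Methods) then fixes the tests: "To evaluate statistical significance of alpha and beta diversities, the Kruskal–Wallis test and permutational multivariate analysis of variance (PERMANOVA) will be performed". Otherwise "continuous variables will be examined by conducting Student’s" t-test or the Mann–Whitney test, with chi-square or Fisher tests for categories. All are named in independent-group form. No pairing, arm-by-time term, restriction of permutations to patients, or distance to a patient's own earlier stool is stated.

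Section 2.3 (Participants) provides three stools per patient: before resection, at the first bowel movement after ileostomy repair, and after the 3-week period. There are 10 patients per arm, allocated by order of enrolment.

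**The concern.** Part of the primary question concerns position relative to a reference: after the course, how does the community compare with the one before the initial surgery? PERMANOVA asks something else, namely whether labelled groups of samples differ by more than random relabelling would produce. A significant result has no sign, so it fits recovery, further departure or an unrelated shift equally well. A non-significant result may mean similarity or merely imprecision. Each patient supplies a personal reference sample, but the named test does not use it as one.

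At stake is the reading of the beta-diversity result, in either direction.

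**Working it through.** The article gives no effect size, variance or power, so there is no figure to reproduce. The check has four parts.

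**1. What enters the test.** With N samples in a groups, PERMANOVA uses

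- SST = (1/N) Σ d²ij over all pairs;
- SSW = Σ over groups of (1/n_g) Σ d²ij over pairs within the group;
- pseudo-F = [(SST − SSW)/(a − 1)] / [SSW/(N − a)].

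Comparing arms on the 20 third stools uses 20×19/2 = 190 distances, and none involves a pre-resection stool. Pooling all 60 stools gives 60×59/2 = 1,770 distances. Of these, 20×20 = 400 link a third stool to a first stool, and only 20 link a patient to their own. Without restricted permutations, those 20 are treated like the rest. Testing third against first stools within each arm does not help either: significance in one arm and not in the other is not a comparison of arms.

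**2. Why there is no direction.** Let s be the post-stoma shift from baseline, and let controls keep all of it. Treated patients keep either 20% or 180%.

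| Treated arm keeps | Squared gap between arm centres | Distance of treated centre from baseline (controls 1.0s) |
|---|---|---|
| 20% (recovery) | (−0.8s)² = 0.64s² | 0.2s |
| 180% (worsening) | (+0.8s)² = 0.64s² | 1.8s |

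With Euclidean distance the two cases are identical to PERMANOVA by construction. The distance from baseline separates them.

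**3. Illustration with a planned measure.** Jensen–Shannon distance, 10 per arm, 300 runs, 499 permutations. Assumed: 60 taxa, between-patient SD 1.0 and sample noise SD 0.4 on the log scale, and a common disturbance of ±1.6 on 20 taxa. PERMANOVA compares arms on the third stool. The alternative is a Mann–Whitney test between arms on the change, second to third stool, in distance to the patient's own first stool.

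| Treated patients (assumed truth) | PERMANOVA p<0.05 | Own-baseline distance p<0.05 |
|---|---|---|
| No effect | 5.0% | 2.7% toward, 1.7% away |
| Return to baseline | 100% | 100% toward |
| Move equally far away | 100% | 100% away |
| Shift in an unrelated direction | 99.7% | 82% away |
| Return from an individual disturbance (SD 1.0) | 9.7% | 100% toward |

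Monte Carlo standard errors are √(0.05×0.95/300) = 1.3 points for the null row, √(0.097×0.903/300) = 1.7 for the 9.7% and √(0.82×0.18/300) = 2.2 for the 82%. In the last row the arms differ in spread rather than in assumed centre, which is why a dispersion check belongs beside PERMANOVA.

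Sequential allocation adds a further point. With an assumed pre-existing arm difference of 2 or 3 SD on one of 20 axes and no treatment effect, PERMANOVA on the third stools rejected in about 60% and 96% of runs. ANCOVA on own-baseline distance stayed at about 5–6%. Using each patient as their own reference removes stable arm differences of this kind, but not all confounding.

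**4. What a null result could mean.** For a standardized difference of 1.25 with 10 per arm, power = Φ(1.25×√(10/2) − 1.96) = Φ(0.835) ≈ 0.80 (two-sided 0.05, normal approximation). For a difference of 1.0 it is 0.61. The 95% CI half-width is about 1.96×√(2/10) = 0.88 SD. Non-significance is therefore compatible with large differences.

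**The case against.** A reader might infer that the plan cannot answer whether dysbiosis is alleviated. The documents do not support that. The Background describes "gut dysbiosis characterized by a reduced diversity of bacteria, an increase in pathogenic bacteria, and a decrease in beneficial bacteria", and section 2.5 plans diversity indices and beneficial/harmful proportions that match this description and have a direction.

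A reader might also infer that a non-significant comparison of third with first stools will be reported as restoration. The article says no such thing; it is only a foreseeable misreading.

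Further objections have weight:

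- **The stated aim.** The Background asks whether intake could influence composition and diversity, a non-directional question that PERMANOVA suits. This stands, and is a reason to keep the test. It does not cover the comparison with the pre-surgery composition that section 2.5 adds.
- **Detail held elsewhere.** The article is condensed, its microbiota methods refer to a published procedure, and any analysis plan is not shown. Pairing may be specified there, and the listed two-sample tests could be applied to within-patient distances. This limits the weight of the point. Even so, the article names a test for beta diversity that does not measure what section 2.5 asks.
- **The simulation.** Equal rejection under symmetric shifts is built in, and the percentages depend on assumed effects. This stands; only the qualitative result carries over.
- **The alternative measure.** Distance to own baseline has its own ambiguity. An unrelated shift registered as away in 82% of runs, and the eight administered strains (section 2.4) could increase the distance by appearing in the stool. This stands, and argues against making distance the sole endpoint or replacing PERMANOVA.

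**Conclusion.** The point holds for beta diversity only. PERMANOVA as named gives neither direction nor distance to the patient's own pre-resection stool, so it leaves unanswered how the composition after the course differs from that before the initial surgery. This follows from the method and needs no assumed effect size. How often it would mislead in this trial cannot be determined from the article; the simulated rates are illustrative.

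Alleviation is still addressed at group level by alpha diversity and the beneficial/harmful proportions. In a 20-patient pilot that acknowledges its non-randomized, exploratory design, this is a worthwhile improvement to the analysis, not a defect that invalidates the trial.

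**What to change.** Alongside PERMANOVA, specify for each patient D31, the distance from the third stool to their own first stool, and D21, the distance from the second to the first. Use generalized UniFrac and repeat with Jensen–Shannon. Compare arms by ANCOVA, D31 = α + β·arm + γ·D21 + error, and report β with a 95% CI; with the synbiotic arm coded 1, a negative β means closer to the pre-resection composition. A Mann–Whitney test on D31 − D21, with an interval for the shift, is an acceptable alternative.

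If PERMANOVA is run across time points, use an arm-by-time term with permutations that respect patient, and add a dispersion check. State that a larger distance may reflect carry-through of the administered strains, that it will be read together with the diversity indices and the beneficial/harmful proportions, and that p>0.05 will not be taken as evidence of restoration.

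The cost is analysis code and a short addition to the analysis plan, or an amendment by the route in section 2.9 if it goes into the protocol. No new stools, assays or distance measures are needed. The Trial Status section reports final stools from 55% of participants at 28 August 2025 (11 if the base is the planned 20), so on that status the contrast can be fixed before the data are complete.

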## Figures and Tables

**Figure 1 jcm-14-07190-f001:**
[figure not shown]
Flow diagram of the study protocol.

**Table 1 jcm-14-07190-t001:** Schedule of assessments, interventions, and follow-up.

	Study Period			
	Enrolment	Post-Allocation		Close-Out
Time Point	t1	t2 (Before Rectal Resection)	t3 (After Ileostomy Repair)	t4 (Outpatient Visit)
Enrolment:				
Eligibility screen	X			
Informed consent	X			
Allocation	X			
Interventions:				
Probiotic intake				
Standard care				
Assessments:				
Fecal testing		X	X	X
Serum laboratory test *	X		X	X

* Complete blood count (neutrophil, monocyte, lymphocyte, hemoglobin, platelets), albumin, and C-reactive protein.

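### Inflammatory-marker change is to be compared between arms without adjustment; t4 adjusted for the post-repair (t3) value would be more precise and needs no new data

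*Protocol article*

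**What the plan says.** Section 2.5 of the protocol article lists inflammatory markers among the secondary outcomes: "Changes in inflammatory markers will be analyzed by comparing various ratios of neutrophils, lymphocytes, albumin, and C-reactive protein". It gives the purpose as "to explore the potential anti-inflammatory effects of probiotics following ileostomy repair". It does not say which visit the change is taken from, or whether the quantity compared is a difference, the final value or a baseline-adjusted value.

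The row "Serum laboratory test" in Table 1 is marked at t1 (enrolment), at the column headed "t3 (After Ileostomy Repair", and at t4 (outpatient visit). No blood test is scheduled between the rectal resection and the repair.

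Section 2.3 fixes the sequence around t3. For stool, "the second fecal test will be performed during the first bowel movement after ileostomy repair". Then "Patients in the experimental group will take probiotics for 3 weeks starting from the second fecal test", while "patients in the control group will be observed for 3 weeks without taking probiotics". The first 10 enrolled patients form the product arm and the next 10 the control arm. The interval to reversal depends on whether chemotherapy is needed.

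For continuous variables, section 2.8 names Student's t-test or the Mann–Whitney test. It names no covariate adjustment.

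**The concern.** The outcome is worded as a change, and neither earlier blood test is a good value to subtract. t1 lies before the resection and before any chemotherapy given between resection and repair, at an interval that differs between patients. t3 is close to the start of the product but comes after surgery, when C-reactive protein, albumin and white-cell ratios can be expected to be disturbed.

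Two things are at stake. First, if the t3-to-t4 difference goes straight into a two-sample test, between-patient variation in the postoperative value enters the comparison at full weight. With 10 patients per arm, lost precision matters. Second, markers can be expected to fall between t3 and t4 in both arms as patients recover. A fall in the product arm, looked at alone, could be mistaken for an anti-inflammatory effect.

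**Working it through.** **Plan's own figure.** There is none to reproduce. The article says no sample size calculation was done, and it gives no SD, correlation or effect size for any marker.

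**Does shared recovery bias the arm comparison?** Let recovery lower a marker by R in both arms and let the product lower it by a further d. The product-arm change is −(R + d), the control change is −R, and their difference is −d. R cancels. Within the product arm, however, recovery makes up R/(R + d) of the fall. With an illustrative d = 0.5:
- R = 1: 1/1.5 = 67%
- R = 3: 3/3.5 = 86%
- R = 5: 5/5.5 = 91%

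**How much noise does the raw change add?** Set the t4 SD to 1, the t3 SD to k and the t3–t4 correlation to r. Both k and r are assumptions.
- Raw change: V_c = k² + 1 − 2rk
- t4 alone: V_4 = 1
- t4 adjusted for t3: V_a = 1 − r²

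Since V_c = (k − r)² + (1 − r²), the ratio V_c/V_a = 1 + (k − r)²/(1 − r²). It is never below 1, and equals 1 only when k = r. Values of V_c/V_a:

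| k | r = 0 | r = 0.2 | r = 0.4 | r = 0.6 |
|---|---|---|---|---|
| 1 | 2.00 | 1.67 | 1.43 | 1.25 |
| 1.33 | 2.77 | 2.33 | 2.03 | 1.83 |
| 1.67 | 3.79 | 3.25 | 2.92 | 2.79 |
| 2.5 | 7.25 | 6.51 | 6.25 | 6.64 |

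For example, k = 1 and r = 0.6 gives (1 + 1 − 1.2)/(1 − 0.36) = 0.80/0.64 = 1.25. With k = 2.5 and r = 0 it is (6.25 + 1)/1 = 7.25.

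The row k = 1 belongs in the range. On the log scale, a proportional postoperative rise moves the mean and leaves the SD unchanged.

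**In terms of power.** With 10 per arm, two-sided 5% (the article does not state sidedness) and 80% power, the noncentral t with 18 degrees of freedom gives a detectable difference of 1.325 t4-SDs for t4 alone. For the raw change, multiply by √V_c. For ANCOVA, use 17 degrees of freedom and √V_a. Power is at a true effect of 1.325 t4-SDs.

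| k, r | Detectable: change | Detectable: ANCOVA | Power: change | Power: ANCOVA |
|---|---|---|---|---|
| 1, 0 | 1.87 | 1.33 | 51% | 80% |
| 1, 0.5 | 1.32 | 1.15 | 80% | 90% |
| 2, 0 | 2.96 | 1.33 | 24% | 80% |
| 2, 0.5 | 2.29 | 1.15 | 37% | 90% |

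The raw change is also noisier than t4 alone whenever r < k/2. At k = 2 or more, that is every r below 1.

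**Cost of adjusting.** Estimating p covariate slopes in 20 patients inflates the expected variance by about 1 + p/(17 − p), if the covariates do not differ systematically between arms. That is 1 + 1/16 = 1.06 for t3 alone and 1 + 2/15 = 1.13 for t1 and t3. Both are below 1.25, the smallest ratio in the first table. The second table reflects the lost degree of freedom but not this inflation.

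**The case against.** The strongest objection is that the article never says change runs from t3. Blood is also taken at t1, and the named tests would suit a plain t4 comparison equally well. The reference visit, transformation and covariates for a secondary laboratory outcome are usually left to a full protocol or SAP, and neither is shown. This stands: an unnamed reference visit is not in itself a finding. What remains is what the article does fix, namely an outcome worded as change and unadjusted two-sample tests. Adjusting t4 for a value already collected improves on a raw change from t3. A change from t1 would be no better placed, for the timing reasons given under the concern.

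A reader might also infer more than the text supports:

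- *That the planned comparison mainly measures surgical recovery.* This is true at most of a within-arm change. Controls have the same operation and the same observation period, so common recovery drops out of the arm difference.
- *That a within-arm fall will be tested or claimed as an effect.* No paired or within-arm test is named, and the stated question is the relation between intake and markers. This calls for a caution, not a correction.
- *That the t3 blood is drawn on a day that follows bowel recovery.* Only the stool sample is tied to the first bowel movement. For blood, Table 1 says no more than after repair.
- *That most of the information is thrown away.* This needs a t3 SD clearly above the t4 SD. At k = 1 and r = 0.6 the change score keeps 1/1.25 = 80% of the information.

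Nor is a post-operative t3 sample an error. As the blood visit nearest the start of the product, it is a sensible covariate.

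**Conclusion.** The point holds as one of precision. A raw t3-to-t4 change compared by the named two-sample tests is noisier than a t3-adjusted comparison of t4. The excess is about 1.2 to 7 times the residual variance for assumed SD ratios of 1 to 2.5 and correlations of 0 to 0.6. The direction follows from the algebra. The size cannot be established, because the article gives neither input, and it runs from modest to severe.

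The result treats t3 as unaffected by the product. The article does not state when the t3 blood is drawn relative to the first dose. It also treats recovery as common to both arms, and sequential allocation does not guarantee that. Section 3 already acknowledges selection bias and confounding. Adjusting for t3 addresses measured differences at t3 and does not cure confounding.

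Severity is low. The outcome is an exploratory secondary one in a 20-patient pilot, and the primary microbiota endpoint is untouched.

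**What to change.** State the marker analysis as a comparison of the t4 value between arms by ANCOVA with the t3 value as covariate, using logs for C-reactive protein and each named ratio. Keep t1 as an optional further covariate in a sensitivity analysis only, given 20 patients. Add a sentence that a fall from t3 to t4 within an arm will not be interpreted as a product effect.

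Leave the t3 draw where it is. The first 10 enrolled are the product arm, and by 28 August 2025 70% of 20, or 14 patients, had been enrolled. Moving the draw now would change the reference value for some controls only.

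The cost is a change of wording and one degree of freedom (two if t1 is added), with no new blood test. The wording can still be fixed ahead of much of the control data: at that date final stool samples were in for 55% of 20, or 11 patients.
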